### Procedure for unblinding if needed {17b}

Not applicable: Blinding will not be implemented in this study.

## Data collection and management

### Plans for assessment and collection of outcomes {18a}

#### Primary outcome (proportion of complete referrals)

For the intervention group, the referral status will be digitally recorded. Time intervals from the woman’s initial visit to the facility to when the referral is sent and when feedback is received will be used to calculate the proportion of complete referrals. In the control group, referrals will be managed through routine paper-based procedures. Sixty days after the referral, trained data collectors will review medical records at both the sending and receiving facilities to determine whether feedback was received. The use of a standardised data extraction tool, aligned with the variables used in the DINKNESH referral and follow-up app, will ensure comparability between the two groups.

To further explain the outcome variable, baseline data will be collected from both groups after consent, including sociodemographic information, clinical data, and knowledge of breast cancer. The African Women Awareness of CANcer (AWACAN) tool will be used to assess awareness, health-seeking behaviour, and perceptions. This baseline information will help interpret the primary outcome [23].

#### Secondary outcomes

The time interval between a woman’s first visit to a health facility and her confirmed breast diagnosis, the proportion of internal referrals within the facility, and the proportion of detected early-stage breast cancers will be assessed. These data will be captured through clinical information recorded in the app and the patient’s medical records. The proportions for each of these secondary outcomes will then be calculated.

#### Qualitative assessment

At the end of the trial, after final follow-up data have been collected for the last referred participant, qualitative assessments will be conducted with participants from the intervention arm and health professionals. Semi-structured interviews will explore the experiences of participants and health providers with the DINKNESH referral and follow-up app, including factors influencing its effectiveness, acceptability, sustainability, and scalability. Interviews will be conducted in Amharic with participants, health professionals, and health facility administrators involved in the intervention. The primary aim is to assess the app’s acceptability, identify implementation challenges, and evaluate its potential for sustainability. Thirty interviews will be conducted, with the final sample size determined by data saturation.

### Plans to promote participant retention and complete follow-up {18b}

In this study, retention is conceptualised as compliance with referral recommendations, which is the key outcome of interest. The strategy to maintain adherence focuses on ensuring that participants receive reminder text messages and that facilities receive notifications and patient information without interruption. To support this, health professionals will register more than one phone number for each participant, including the number of a health extension worker. Reminder text messages will be sent to all registered phone numbers. If a participant does not have her own phone, the number of a close relative registered with her consent will be used in addition to the health extension worker’s number. Regular monitoring will be conducted to identify and address any technical issues that may arise in communication between facilities, such as app malfunctions, network interruptions, or data synchronisation problems.

### Data management {19}

To ensure the quality of the data, data collectors and supervisors were trained prior to implementation. Supervisors are overseeing the implementation of the intervention and proper data documentation. A standard operating procedure (SOP) was developed, and all personnel follow it throughout the study. Both qualitative and quantitative data collection tools were pretested. Baseline information is being collected electronically using Research Electronic Data Capture (REDCap) [24]. For the qualitative data, all recorded audio files will be deleted once transcription is finalised. The translated and transcribed data will be stored confidentially and will be accessible only to the study team.

### Confidentiality {27}

All trial-related data including patient demographic information, diagnoses, investigation results, and treatments provided will be stored on password-protected devices. All paper-based records will be kept in locked cabinets. Patient identifiers will be coded, and the code key will be stored separately to ensure confidentiality.

### Plans for collection, laboratory evaluation, and storage of biological specimens for genetic or molecular analysis in this trial or for future use {33}

Not applicable: The study does not include plans to collect or use biological specimens.

## Statistical methods

### Statistical methods for primary and secondary outcomes {20a}

#### Primary outcome (proportion of complete referrals)

All outcome measures will be analysed using IBM SPSS Statistics 25.0. Baseline differences between the intervention and control groups will be assessed using the independent samples *t*-test for continuous variables and the chi-square (χ^2^) test for categorical variables. To assess the effect of the intervention on the proportion of successfully completed referrals, a mixed-effects logistic regression model will be used, adjusting for potential confounders and accounting for clustering at the health facility level. Results will be reported in accordance with the CONSORT guidelines for reporting clinical trials.

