### Sample size {14}

The sample size was calculated following established methods for cluster randomised trials [21]. The calculation aimed to detect an increase in the proportion of complete referrals from 52% (based on a study in Tanzania [22]) to 70% in the intervention group. Using 80% power and a 5% significance level, and assuming an intra-cluster correlation coefficient of 0.01, the sample size was adjusted for clustering. With 8 clusters (4 intervention and 4 control) and equal allocation, the required sample size under individual randomisation was 222. After adjusting for the design effect due to clustering, the total required sample size increased to 282, corresponding to approximately 35 individuals per cluster.

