### Recruitment {15}

All women with self-reported or CBE-detected breast abnormalities are being invited by trained staff at the health facilities to voluntarily participate in the study. Enrolment will continue until the required sample size of 35 participants is reached at each clustered facility. Once the target number is achieved, no additional participants will be included.

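### The planned baseline t-tests and chi-square tests ignore facility clustering, so they overstate imbalance between arms

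*Protocol article*

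**What the plan says.** In section 20a of the protocol article, under the primary outcome, the plan reads "Baseline differences between the intervention and control groups will be assessed using the independent samples" t-test for continuous variables, and names the chi-square test for categorical ones ("test for continuous variables and the chi-square"). No allowance for clustering is attached to either test.

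The next sentence turns to the primary analysis: "a mixed-effects logistic regression model will be used, adjusting for potential confounders and accounting for clustering at the health facility level". The secondary outcome models in the same section are also mixed-effects models with clustering by facility.

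The data to be compared are described in section 18a: "baseline data will be collected from both groups after consent, including sociodemographic information, clinical data, and knowledge of breast cancer". The design facts are in sections 14 and 15: "With 8 clusters (4 intervention and 4 control) and equal allocation, the required sample size under individual randomisation was 222"; "assuming an intra-cluster correlation coefficient of 0.01, the sample size was adjusted for clustering"; "Enrolment will continue until the required sample size of 35 participants is reached at each clustered facility".

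**The concern.** The unit of allocation is the facility. Women attending one facility share a catchment area, staff and a region, so their sociodemographic, clinical and knowledge variables are likely to be correlated. A test that counts women as independent uses a standard error that is too small, and its p-value is then too small as well. The protocol accepts correlation within facilities in its sample size and in every outcome model. Only the baseline comparison leaves it out.

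The baseline comparison carries more weight here than in an individually randomised, blinded trial. Women are enrolled after the facilities were allocated (section 13), and nobody is blinded (section 17a). Staff who know the arm could recruit different kinds of women, and readers will look to the baseline table for signs of this. A p-value that ignores clustering will flag ordinary differences between facilities as if they were differences between arms, so it cannot serve that purpose.

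**Working it through.** **Inputs from the protocol.** Eight facilities, 4 versus 4 (section 14); 35 women per facility (section 15), so 4 × 35 = 140 per arm and 280 in total; ICC 0.01, stated for the outcome (section 14).

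**Inputs that are assumed.** The protocol gives no ICC for any baseline variable. The values 0.02, 0.05 and 0.10 below are assumptions that show a range.

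**The protocol's own clustering figure.** No figure is given for the baseline tests, but the sample size shows that the ICC was applied. With 52% versus 70%, two-sided 5% and 80% power, the unpooled formula gives (1.960 + 0.842)² × (0.52 × 0.48 + 0.70 × 0.30) / 0.18² = 111.3 per arm, or 222 when rounded down. The design effect at 222/8 = 27.75 per cluster is 1 + 26.75 × 0.01 = 1.2675, and 222 × 1.2675 = 281.4, which gives the stated 282. The plan therefore treats women within a facility as correlated.

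**True level of the planned tests.** With m = 35, the variance of a difference between arms is inflated by DE = 1 + (35 − 1) × ICC. A test that ignores this has a true rejection rate of 2 × [1 − Φ(1.96/√DE)] at nominal 5%, when no systematic difference between arms exists.

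The formula was checked with 40,000 simulated trials per ICC (4 versus 4 facilities of 35; a normal variable for the t-test, a binary variable with 50% prevalence for the chi-square). The last column is a t-test on the eight facility means.

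| ICC | DE | 1.96/√DE | Formula | Simulated t-test | Simulated chi-square | t-test on 8 facility means |
|---|---|---|---|---|---|---|
| 0 | 1.00 | 1.960 | 5.00% | 4.94% | 4.95% | 4.98% |
| 0.01 (protocol, outcome) | 1.34 | 1.693 | 9.04% | 8.93% | 8.70% | 4.94% |
| 0.02 (assumed) | 1.68 | 1.512 | 13.05% | 12.88% | 12.75% | 5.05% |
| 0.05 (assumed) | 2.70 | 1.193 | 23.29% | 23.35% | 23.24% | 4.88% |
| 0.10 (assumed) | 4.40 | 0.934 | 35.01% | 35.31% | 35.25% | 4.83% |

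For every 10 baseline variables tested, the expected number flagged without any systematic difference is 10 × 0.05 = 0.5 for a valid test, 10 × 0.0904 = 0.9 at ICC 0.01, and 10 × 0.2329 = 2.3 at the assumed ICC of 0.05. The number of variables is illustrative; the protocol does not state one.

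The test on facility means keeps its level throughout, so the inflation comes from ignoring clustering and not from the small number of facilities.

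**The case against.** The best defence is that these tests decide nothing. They yield no effect estimate and no stated rule depends on them. Section 18a says that the baseline data are there to help interpret the primary outcome, and all outcome models account for clustering. This stands, and it limits the consequence: the primary result can be affected only indirectly.

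Three stronger readings are tempting, and the document does not support them.

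- *That the baseline p-values choose the covariates, so that the primary estimate is compromised.* The baseline sentence stands directly before the one on adjusting for confounders, and a reader might join them. The protocol states no such link. Nothing shown rules it out either, so it is a risk and no more.
- *That the lack of a named covariate list is itself a fault.* A statistical analysis plan may fix the list, and a protocol article commonly leaves it there.
- *That the tests breach the reporting guideline named in the same section ("Results will be reported in accordance with the CONSORT guidelines for reporting clinical trials").* The content of that guideline is not in the document, so this cannot be shown from it.

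It is also fair to say that looking at balance is reasonable in an unblinded trial that recruits after allocation, and that real imbalance may exist. That supports making the comparison; it does not support this method. Finally, only the 9% figure rests on an ICC from the protocol, and even that ICC was given for the outcome. At that value the excess over a valid test is modest.

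**Conclusion.** The stated method is wrong for this design. This is a choice the protocol makes in so many words, not a detail left to another document, and an analysis plan that followed it would carry the error forward. At the protocol's own ICC of 0.01 the baseline tests run at about 9% in place of 5%. If baseline variables cluster more strongly, the level would be about 13%, 23% or 35% at assumed ICCs of 0.02, 0.05 or 0.10.

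The figures assume equal facilities of 35 and take no account of the stratification by facility type. They describe false flags when there is no systematic difference between arms, and do not imply that every flagged difference will be false.

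The consequence is confined to the baseline comparison: it overstates imbalance and cannot tell differential recruitment from ordinary facility variation. The primary analysis is not shown to be invalid.

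**What to change.** Replace the t-test and chi-square sentence in section 20a. Describe baseline characteristics by arm and by facility, with means or percentages and standardised differences, and without p-values. If a formal comparison is wanted, use one that respects clusters, such as a test on the eight facility means. That test has only 4 + 4 − 2 = 6 degrees of freedom, so a non-significant result would not show balance, and the description should carry the weight.

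Add one sentence saying that the adjustment covariates, including the stratification factor facility type, are not chosen on baseline p-values.

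The cost is a small amendment. Section 25 requires approval by both ethics bodies and a report to the registries. No new data are needed and there is less analysis to run. The trial gives up individual-level baseline p-values. Enrolment began on 30 November 2024 and the trial is unblinded, so the sentence on covariates should be settled soon, and the amendment should state what outcome data had been seen by then.

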## Objectives {7}

The primary objective of this study is to evaluate the effectiveness of the DINKNESH referral and follow-up app in enhancing referral completion for women with breast-related abnormalities at primary healthcare settings in Ethiopia, specifically by determining the proportion of successfully completed referrals.

Hypothesis: The use of the DINKNESH referral and follow-up app will increase the proportion of completed referrals from 52% to 70% for women with breast-related abnormalities after undergoing a CBE compared with the routine standard referral process.

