#### Secondary outcomes

Time to diagnosis: The time interval between a woman’s first visit to a health facility and her confirmed breast diagnosis will be measured using clinical records from the app (intervention group) and patient medical records (control group). Descriptive statistics (mean, median, interquartile range, and standard deviation) will be used to summarise the time intervals in both groups. Time to diagnosis will be dichotomised as ≤60 days timely versus >60 days delayed and analysed using multivariable mixed-effects logistic regression adjusting for potential confounders and accounting for clustering at the health facility level.

Proportion of internal referrals and proportion of early-stage breast cancer diagnoses: Descriptive statistics (percentages) will be used to summarise these proportions. Comparisons between the intervention and control arms will be conducted using multivariable mixed-effects logistic regression accounting for clustering at health facility level and adjusting for possible confounders.

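### The mixed-effects logistic model on 8 facilities has no stated small-sample inference; with ordinary large-sample inference its type I error exceeds 5%, slightly at the planned ICC of 0.01

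*Protocol article*

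**What the plan says.** Under Statistical methods {20a} of the protocol article, the primary analysis is described in one sentence: "a mixed-effects logistic regression model will be used, adjusting for potential confounders and accounting for clustering at the health facility level". The secondary comparisons use the same type of model; for dichotomised time to diagnosis this is "multivariable mixed-effects logistic regression adjusting for potential confounders and accounting for clustering at the health facility level". The software is fixed ("All outcome measures will be analysed using IBM SPSS Statistics 25.0"), but the estimator, test statistic and degrees-of-freedom method are not given.

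Sample size {14} sets the number of randomised units: "With 8 clusters (4 intervention and 4 control) and equal allocation". It also sets the error rates and the clustering assumption: "Using 80% power and a 5% significance level, and assuming an intra-cluster correlation coefficient of 0.01". No source is given for the ICC. Recruitment {15} stops at 35 women per facility. Sequence generation {16a} stratifies by facility type, with two primary hospitals and six health centres.

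**The concern.** The treatment effect is a contrast between facilities. With four per arm, the between-facility variance rests on 8 − 2 = 6 degrees of freedom, or 5 once facility type is in the model. Two things then go wrong with ordinary inference from a random-intercept logistic model. Maximum likelihood pulls the facility variance towards zero, and often to exactly zero. The estimate is then compared with a normal reference, or a t reference on hundreds of residual degrees of freedom, as if that variance were known. Both make intervals too narrow and the test too liberal.

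The stake is the trial's single primary comparison. Allocation is open, and the Discussion expects the result to inform policymakers. The choice of reference distribution could by itself decide significance, so it should not be made after the data are seen.

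**Working it through.** **Inputs.** Sample size {14}: 4 versus 4 clusters, 5% significance, 80% power, ICC 0.01, 52% versus 70%. Recruitment {15}: 35 per cluster. Sequence generation {16a}: stratification by facility type. Assumed: a two-sided test, one hospital in each arm, and ICCs other than 0.01.

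**Step 1: the plan's own figure.** With normal quantiles and unpooled variances:

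n per arm = (1.960 + 0.842)² × (0.52×0.48 + 0.70×0.30) / 0.18² = 111.3, or 222.7 in total (stated 222).

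Design effect = 1 + (222/8 − 1) × 0.01 = 1.2675; 222 × 1.2675 = 281.4, so 282 (stated 282).

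The figures reproduce with normal quantiles, so the planning makes no allowance for 6 between-cluster degrees of freedom.

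**Step 2: type I error.** Trials were simulated under no effect: 8 clusters of 35, 52% in both arms, beta-binomial clustering. There were 4,800 trials per ICC without covariates and 6,000 with facility type. The Monte Carlo standard error is about 0.3 to 0.5 points. Rejection rates at nominal 5%:

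| Analysis | ICC 0.01 | 0.02 | 0.05 | 0.10 |
|---|---|---|---|---|
| Mixed logistic, maximum likelihood, Wald z | 6.5% | 9.2% | 12.0% | 14.3% |
| Mixed logistic, REML-type quasi-likelihood, z | 5.4% | 7.4% | 8.7% | 9.8% |
| Maximum likelihood, z, plus facility type | 7.9% | 10.1% | 13.8% | not run |
| REML-type, z, plus facility type | 6.0% | 7.3% | 8.9% | not run |
| t-test on 8 facility proportions, 6 df | 5.0% | 5.2% | 5.4% | 5.8% |

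Replacing z by t on 278 residual degrees of freedom (280 women minus two coefficients) changes the REML-type row by at most 0.2 points. At ICC 0 the mixed model is not inflated (3.9% to 4.5%). At ICC 0.01 the fitted facility variance was zero in about 57% of maximum-likelihood fits and 37% of REML-type fits. A cluster-level linear model with arm and facility type on 5 degrees of freedom also holds about 5%.

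**Step 3: analytic check.** A normal critical value of 1.960 applied to a t statistic rejects 9.8% of the time on 6 degrees of freedom and 10.7% on 5. This is the approximate size when facility variation dominates and its variance is estimated without bias. Maximum likelihood adds to it.

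**Step 4: power of a valid test with 35 per cluster.** At ICC 0.01 the design effect is 1 + 34 × 0.01 = 1.34.

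SE = √[1.34 × (0.2496 + 0.2100) / (4 × 35)] = 0.0663; noncentrality = 0.18 / 0.0663 = 2.71.

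- 6 df (critical value 2.447): about 62%, confirmed by simulation.
- 5 df (critical value 2.571): about 59%.
- Normal reference: Φ(2.71 − 1.96), about 77%.

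At ICC 0.05 the design effect is 2.70, the SE 0.0941 and the noncentrality 1.91. Power is then about 36% on 6 df and 34% on 5 df.

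**The case against.** The strongest reply is that the faulted test is not in the document. The article names a model, an adjustment, a clustering level and a software package. It does not name maximum likelihood, a Wald z statistic or residual degrees of freedom. A degrees-of-freedom method is the kind of detail that an unseen analysis plan may hold, and nothing in the text rules one out. This stands, and it makes the point conditional. A reader might infer that the trial's p-value will be wrong; the documents do not support that.

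The second reply concerns size. The only ICC in the document is 0.01. There the excess is small, and the lowest figure (5.4%) is within Monte Carlo error of 5%. A reader might carry away a false-positive rate of 10% to 14%. Those figures need either a higher ICC that the document does not state or the least favourable estimator, and usually both. This also stands. A higher ICC is plausible, because Outcomes {12} makes completion depend on feedback returned by the receiving institution, but the document gives no estimate.

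Third, a reader might say that the model treats some 280 women as independent. It does not: a random intercept widens the standard error by the estimated facility variance. The fault is the poor estimate of that variance and the reference distribution.

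Fourth, a reader might object that an odds ratio does not estimate the hypothesised 52% to 70% difference. That is a preference about reporting. The logistic model tests the same null of no difference.

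What the reply does not remove is that the named model, run with ordinary inference on 8 facilities, does not hold 5%, and that the sample size was built on the same large-sample logic.

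**Conclusion.** The point holds in its conditional form. With ordinary large-sample inference, the planned model on 4 versus 4 facilities has type I error of about 5.4% to 7.9% at ICC 0.01 and about 9% to 14% at ICCs of 0.05 to 0.10. These figures rest on equal clusters of 35, a 52% null proportion, beta-binomial clustering and two-sided testing. The higher ICCs are assumptions. The documents do not establish that the primary test is invalid as it will be run, only that its inference is left open where the choice matters.

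The correction exposes a further consequence. A test that holds 5% has about 59% to 62% power at the protocol's own ICC, so 8 facilities of 35 women do not deliver both stated error rates.

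**What to change.** Before analysis, state one inference method for the primary outcome and exclude z and residual degrees of freedom. Either:

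- compare the 8 facility completion proportions in a linear model with arm and facility type, with a t reference on 5 degrees of freedom, and report the risk difference with its 95% confidence interval; or
- keep the mixed logistic model with a named small-sample degrees-of-freedom correction tied to the number of clusters, for example Satterthwaite. This version was not simulated here. Simply referring the mixed-model statistic to t on 6 df is conservative at ICC 0.01 (2.1% to 2.5%), so the exact method must be named.

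For the early-stage cancer outcome, use the corrected mixed model. The denominator is detected cancers, and some facilities may have none, which would leave their proportion undefined.

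A permutation test alone is not enough. If each arm received one hospital, the stratified lottery has 2 × 20 = 40 allocations, and the smallest two-sided p-value is 2/40 = 0.05.

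The change needs wording only, with no new data. Its price is wider intervals and a lower stated power: about 59% (5 df) to 62% (6 df) for 52% versus 70% at ICC 0.01. Sample size {14} should be restated accordingly.
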